### Plans to give access to the full protocol, participant-level data, and statistical code {31c}

The full protocol (including the data-management and statistical-analysis plans) and the statistical code will be available on request from [name]. Parts of the data sets will be published with open access according to data-protection regulations. More data will be accessible on request from [name].

### Composition of the data monitoring committee, its role, and reporting structure {21a}

The team from the coordinating centre will monitor the data.

### Adverse event reporting and harms {22}

The study participants will be requested to immediately inform the local research worker (if possible) about serious adverse events. The occurrence of serious adverse events will be recorded, at the latest, at the next follow-up assessment. Subsequently, all serious adverse events will be reported to the coordinating centre in Ulm using standardised forms.

Community-based treatment, as intended in GBV, might lead to higher burden on relatives, and therefore, the burden on relatives was chosen as secondary outcome. No other adverse events are expected from trial participation.

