### Additional consent provisions for collection and use of participant data and biological specimens {26b}

Informed consent includes consent for using data from the statutory health insurance.

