### Outcomes {12}

All outcomes will be assessed over 24 months at 6-month intervals: *t*_0_, *t*_0_ + 6 months (*t*_1_), *t*_0_ + 12 months (*t*_2_), *t*_0_ + 18 months (*t*_3_), *t*_0_ + 24 months (*t*_4_).

The primary outcome is change in empowerment (EPAS, mean total score) [14] over 24 months. This outcome was chosen because contemporary care for people with permanent severe mental illness is aimed not only at controlling disease symptoms but also at empowering patients by increasing their capacities for a largely independent lifestyle and comprehensive social and professional inclusion.

The secondary outcomes include changes over 24 months in (1) satisfaction with psychiatric treatment using the Questionnaire of Treatment Satisfaction (ZuF8, sum score) [15, 16], (2) subjective quality of life using the World Health Organisation Quality of Life—short version (WHO-QoL-BREF, mean score rescaled to the range between 0 and 100) [17], (3) count of unmet needs for psychiatric and psychosocial services using the Camberwell Assessment of Need—European version (CAN) [18, 19], and (4) psychosocial and clinical impairment using the Health of the Nation Outcome Scale (HoNOS, sum score) [20–23]. Furthermore, the cost-utility of the GBV treatment in comparison to CAU will be investigated from the societal perspective and from the perspective of the statutory health insurance (payer perspective). Costs will be estimated from the view of the statutory health insurance and of the national economy using the Client Sociodemographic and Service Receipt Inventory (CSSRI) [24]. The cost-utility ratio is defined as the costs of gaining a “healthy” year of life (QALY), measured by the Euro Quality of Life—5 dimensions questionnaire (EQ-5D) [25].

The secondary outcomes assessed in informal caregivers will be changes over 24 months in (1) the perceived burden related to support of patient suffering from serious mental illness using the Involvement Evaluation Questionnaires (IEQ-EU, sum score) [26], (2) satisfaction with the patient’s psychiatric treatment using the ZuF8 (sum score) [15, 16], and (3) subjective quality of life using the WHO-QoL-BREF (mean score rescaled to the range between 0 and 100) [17].

The participants are asked to immediately report serious adverse events. Inpatient stays will be recorded at the next follow-up assessment, at the latest, by completing the CSSRI.

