### Sample size {14}

The calculation of the expected effect size is based on the results of a previous study (IVPOWER) [10]. Since the total score of the scale for measuring empowerment in patients with affective and schizophrenic disorders (EPAS) as the primary outcome proved to be rather difficult and slow to change, a low effect size of 0.20 and a high power of 0.90 were chosen for the sample size calculation of the present study.

The sample size calculation was based on a linear mixed-effects regression model with an interaction effect between study group and measurement time. The expected effect size, alpha value, beta value, number of measurements, number of study sites, and expected number of dropouts over all follow-up measurements were taken into account.

Based on the results of the IVPOWER study, an increase in the effect size of the primary outcome parameter is expected, from 0 standard deviations (SD) at baseline (*t*_0_) to 0.2 SD at the last assessment (*t*_4_). Furthermore, a decreasing dropout rate of 15% between *t*_0_ and *t*_1_, 7% between *t*_1_ and *t*_2_, 4% between *t*_2_ and *t*_3_, and 2% between t_3_ and t_4_ is expected, so that the expected sample size at *t*_4_ still comprises 72% of the initial sample.

A sample size calculation using the Web-based programme RMASS (www.rmass.org) yielded a number of at least 978 subjects for twelve study sites. On this basis, the target sample size was set at 1000 participants.

We expect to include about 350 informal caregivers, of whom about 225 will complete the study based on the experience gained in the IVPOWER study (recruitment rate = 36.8%; dropout rate = 35.6%).

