The primary outcome will be measured by means of the EPAS, which measures empowerment as the patient’s perceived possibilities to control his or her own life on five dimensions: daily living, social relationships and sexuality, psychiatric treatment, hope and self-efficacy and self-esteem. This self-assessment instrument has 33 items and five additional items each for patients who are employed and for patients with minor children. Cronbach’s *α* = 0.94 was obtained for the total scale [14]. Originally developed to assess empowerment in patients with affective and schizophrenic disorders, the EPAS has also proved to be reliable in patients with other types of severe mental disorders [10, 28].

The German short version of the Client Satisfaction Questionnaire (CSQ8), published as Fragebogen zur Patientenzufriedenheit (ZUF8) [15, 16], is a suitable tool for measuring patient satisfaction with their mental health care.

The WHO-QoL-BREF captures the patients’ subjective quality of life in the dimensions of physical health, mental well-being, social relationships, and environmental conditions. The WHO-QoL-BREF is a self-assessment tool with 25 items [17].

The CAN records patients’ perceived needs and the extent to which they are met, covering 23 areas. No special knowledge is required to work with this instrument [18, 19].

The HoNOS measures the clinical and psychosocial impairment of patients in twelve dimensions, independent of diagnosis. After an appropriate briefing, members of all mental health professions can carry out the HoNOS assessment [20–23].

The EQ-5D enables the assessment of health conditions as a basis for determining quality-adjusted life years (QALY) [25].

The use of health and psychosocial care services will be recorded using the CSSRI [24]. Health care costs are estimated by multiplying the service units used by the billing costs per unit for a 6-month period. For the health economic analysis from the perspective of statutory health insurance, expenditures will be determined on the basis of billing data.

The German version of the Involvement Evaluation Questionnaire (IEQ-EU) [11] will be used to assess the burden on informal caregivers.

To assess treatment satisfaction and subjective quality of life, the same instruments will be used for informal caregivers as for patients, specifically the ZUF8 [15, 16] and the WHO-QoL-BREF [17].

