Dropouts and adverse events will be documented on standardised forms at the next follow-up assessment, at the latest.

Only trained GBV team members will administer the EPAS, CAN, and HoNOS and lead the enrolment procedure. A contact person at the coordinating centre will be available to GBV team members throughout the course of the study to answer questions on participant enrolment and screening. Refresher trainings will be offered as needed.

All local research workers have been trained and will follow uniform standard operating procedures (SOP) as to good clinical practice (GCP), recruitment, assessment, and questionnaires, for example. Advanced training sessions (e.g. training in HoNOS evaluation) of the research associates will be part of biannual project meetings. During the study, local research workers will be regularly tested for interrater reliability on the HoNOS and CAN using case vignettes.

Research workers at the coordinating centre will check the quality of data collection at each site during semiannual monitoring visits. The results will be documented in a monitoring report, which will be sent back to the local research workers and considered for the final analysis and interpretation of the data. The focus of the monitoring will primarily be on site monitoring, i.e. whether the local research workers are conducting the study in accordance with the given SOP. Furthermore, the monitoring will involve checking the completeness and plausibility of the available study documents. During the 1-year recruitment phase, the inclusion of study participants in accordance with the study protocol will be checked (e.g. by checking their eligibility and informed consent). Thereafter, the monitor will focus on the completeness and plausibility of the collected data and the documentation of serious adverse events. In addition, the monitor will offer support in case of questions or ambiguities in terms of participant recruitment, study conduct, and data collection and reporting, thus contributing to increased data quality.

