## Discussion

This is the first RCT in Germany to examine the effectiveness and efficiency of integrated mental health care compared to CAU. This multicentre study will evaluate the impact of a community-based mental health care concept (GBV) on empowerment, quality of life, treatment satisfaction, and health economic measures among people suffering serious mental illnesses. The results of this study will help to decide whether GBV should be integrated into routine care for people with mental illness and financed by the statutory health insurance in the future.

A major strength of this study is the RCT design, which is recognised as the gold standard for examining the efficacy of interventions. High levels of academic rigour will be maintained throughout the data collection, data management, and data analysis by the involvement of independent, trained research associates and the use of standardised, validated scales. An additional strength is that the study will be conducted at different locations in Germany covering a broad range of catchment areas with different levels of urbanisation, different local mental health service systems, and different service providers. This will be advantageous when it comes to generalisation of the study results. In contrast, randomisation reduces the willingness to participate and therefore may lead to a selection effect. Another strong point of this study design is the economic evaluation from both national economic and statutory health insurance views. Patient reports on service use will provide the basis for estimating disease-related costs independently of funding agencies. In addition, health insurance claims data will be used to assess real costs for statutory health insurance.

The integrated care concept has been refined based on the results of the previous IVPOWER-study, which examined the efficacy of integrated care according to network mental health contracts. Fundamental changes were made with regard to participant enrolment and to the comparability of services across sites. An initial standardised assessment process regarding empowerment, unmet care needs, and psychosocial functioning was introduced to verify the need for such a comprehensive form of care by all community-based mental health service providers. Moreover, quality standards for GBV were set, and training activities across service providers were organised.

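### Serious adverse events and inpatient stays after a participant's last attended visit have no assured route into the record, and the claims data that could fill much of the gap are assigned only to costs

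*Protocol article*

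**What the plan says.** Adverse event reporting and harms {22} gives a first route, "The study participants will be requested to immediately inform the local research worker (if possible) about serious adverse events", and then a deadline, "The occurrence of serious adverse events will be recorded, at the latest, at the next follow-up assessment". Outcomes {12} treats hospital care the same way: "Inpatient stays will be recorded at the next follow-up assessment, at the latest, by completing the CSSRI". Plans for assessment and collection of outcomes {18a} repeats the deadline and applies it to dropouts too: "Dropouts and adverse events will be documented on standardised forms at the next follow-up assessment, at the latest". The Discussion makes clear that service use is self-reported: "Patient reports on service use will provide the basis for estimating disease-related costs independently of funding agencies".

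Insurer data are available in principle for every patient. Membership of a participating insurer is an inclusion criterion (Eligibility criteria {10}), and section {26b} states: "Informed consent includes consent for using data from the statutory health insurance". The use given for these data is economic: "For the health economic analysis from the perspective of statutory health insurance, expenditures will be determined on the basis of billing data". The Discussion likewise names only insurer costs, and no safety use is stated.

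Sample size {14} expects dropout of 15%, 7%, 4% and 2% over the four intervals, so that the sample at t4 "still comprises 72% of the initial sample".

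**The concern.** The deadline works only if there is a further attended visit. A participant who dies, disengages or remains too unwell to be seen has none, and these are plausibly the people with a higher event rate. A deceased participant cannot self-report. No second source is named: not treating clinicians, GBV staff, informal caregivers or insurer records.

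There is also a possible imbalance. Research workers who collect data are unblinded (Who will be blinded {17a}), and only GBV brings continuous case-manager contact and a round-the-clock crisis service. If staying in the study, or being prompted to report, differs between arms, recorded event counts could differ when true rates do not.

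At stake is how complete and comparable the record of admissions and serious events is. The Background gives unnecessary admissions as one motive for integrated care, so readers will want to see admissions by arm. The primary empowerment analysis is not affected.

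**Working it through.** **Inputs.** Dropout by interval of 15%, 7%, 4% and 2%, 72% remaining at t4, and a target of 1000 participants (Sample size {14}). Visits every 6 months to 24 months (Outcomes {12}).

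**Step 1: reproduce the plan's figure.** If the percentages refer to the initial sample, retention at t4 is 1 − (0.15 + 0.07 + 0.04 + 0.02) = 0.72, which matches. Compounded, it would be 0.85 × 0.93 × 0.96 × 0.98 = 0.744, which does not. The first reading is therefore the plan's own, and the second is kept as a sensitivity case.

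**Step 2: participants without a t4 visit.** 1000 × 0.28 = 280, or about 256 if compounded. Of these, 150 never attend any follow-up.

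**Step 3: person-time with no later visit.** Assume that dropouts do not return and that events are captured only up to the last attended visit. The covered share is then the mean retention over the four visits:

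- Additive: (0.85 + 0.78 + 0.74 + 0.72) / 4 = 0.7725. Uncovered share 0.2275, which is 0.2275 × 24 = 5.46 months per participant, or 5,460 of 24,000 person-months.
- Compounded: (0.850 + 0.791 + 0.759 + 0.744) / 4 = 0.786. Uncovered share about 0.214.

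Both are upper bounds. They allow no report between visits, and they count time after death or withdrawal as time at risk.

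**Step 4: could this distort a comparison between arms?** Take equal, constant true event rates and no reports outside visits. Scale the planned dropout by a factor k in each arm, so that the captured share is 1 − k × 0.2275. The ratio shown is the arm with less dropout over the arm with more.

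| Dropout by t4, two arms | Captured shares | Apparent rate ratio |
|---|---|---|
| 28% and 28% | 0.7725 and 0.7725 | 1.00 |
| 23% and 33% (k = 0.82, 1.18) | 0.813 and 0.732 | 1.11 |
| 18% and 38% (k = 0.64, 1.36) | 0.854 and 0.691 | 1.24 |
| 14% and 42% (k = 0.50, 1.50) | 0.886 and 0.659 | 1.35 |

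The arm-specific dropout rates are assumptions. The article gives none.

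**The case against.** The strongest reply is that the gap is smaller than it looks. Immediate reporting comes first and the visit is only the latest point. Events before the last attended visit are captured, visits take place wherever the participant prefers, dropouts have their own form, and monitoring covers the documentation of serious events. Billed hospital stays of dropouts may already be in the claims data, though not classed as adverse events. All of this stands, and it is why the figures above are ceilings. None of it supplies an assured route: immediate reporting is qualified by feasibility, the content of the dropout form is not shown, and no source is named that would reveal an event nobody reported.

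A reader might infer that events in dropouts are lost, or that ascertainment differs between arms. The documents support neither. The first is too absolute for the reasons just given. On the second, the reporting rule is the same for both arms, and no section makes the case manager or the crisis service a reporting route. With equal dropout and equal reporting the apparent ratio stays at 1.00.

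Two further objections have weight. Admissions and deaths are not listed outcomes, so the remedy adds a table and does not repair a stated analysis. The article also condenses a full protocol that may name other sources. Even so, the harms section does state a route and a deadline, and that rule depends on a visit.

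**Conclusion.** The point holds in a limited form. As stated, serious adverse events and inpatient stays rest on participant report with the next follow-up as the only backstop, so events after the last attended visit have no assured way of being recorded. On the plan's own dropout this concerns up to about 28% of participants by t4 and at most about 21–23% of planned person-time.

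Differential ascertainment is a possibility only. Apparent ratios of about 1.1 to 1.35 require assumed dropout gaps of 10 to 28 percentage points, and neither a gap nor its direction is shown. This is an inexpensive improvement to the safety record. It does not threaten the primary result.

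**What to change.** In Outcomes {12} and Adverse event reporting and harms {22}, specify that all-cause and psychiatric inpatient admissions and inpatient days are also tabulated by randomised arm from the claims data already planned for the payer cost analysis. Add deaths if the insurer extract contains them. Include all randomised participants, with dropouts who have not withdrawn data consent, and censor at the end of insurance membership or at withdrawal of data consent. Keep the serious adverse event forms for narratives and for events outside hospital.

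If the extract holds the needed fields, the cost is one additional specification and one table. Claims arrive late and miss events without billed hospital care, so they supplement the forms and do not replace them. Three things must be confirmed first: that the extract carries admission dates and diagnoses, whether it records deaths, and that consent to insurer data continues after a participant leaves study follow-up.

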### Frequency and plans for auditing trial conduct {23}

There are no plans for independent trial auditing.

### Plans for communicating important protocol amendments to relevant parties (e.g. trial participants, ethical committees) {25}

Any modifications to the protocol which may impact the study’s conduct or the potential benefit to the participants or which may affect participant safety will require a formal amendment to the protocol. Important protocol amendments must be submitted to local ethical committees and be communicated to all directly involved parties, specifically the umbrella association of community psychiatry (Dachverband Gemeindepsychiatrie), the local mental health care providers, the statutory health insurances, and the Institute for Epidemiology and Medical Biometry at Ulm University, which will randomise the participants. The entry at the German Clinical Trial Register DRKS00019086 is kept updated.

## Dissemination plans {31a}

The research results will be disseminated in peer-reviewed journals, together with anonymised data, where possible. Moreover, the results will be shared through oral and poster presentations at international conferences and at national stakeholder events. All project partners are encouraged to contribute to the dissemination of project outcomes. The researchers employed at the University of Ulm will lead the scientific dissemination of the study results. Authorship will provide credit for the researcher's contributions to the study and will carry accountability.

A project report in plain language will be sent to all participants and will be accessible on the project’s website. The only publication restrictions involve the national data-protection regulations.

## Discussion

This is the first RCT in Germany to examine the effectiveness and efficiency of integrated mental health care compared to CAU. This multicentre study will evaluate the impact of a community-based mental health care concept (GBV) on empowerment, quality of life, treatment satisfaction, and health economic measures among people suffering serious mental illnesses. The results of this study will help to decide whether GBV should be integrated into routine care for people with mental illness and financed by the statutory health insurance in the future.

A major strength of this study is the RCT design, which is recognised as the gold standard for examining the efficacy of interventions. High levels of academic rigour will be maintained throughout the data collection, data management, and data analysis by the involvement of independent, trained research associates and the use of standardised, validated scales. An additional strength is that the study will be conducted at different locations in Germany covering a broad range of catchment areas with different levels of urbanisation, different local mental health service systems, and different service providers. This will be advantageous when it comes to generalisation of the study results. In contrast, randomisation reduces the willingness to participate and therefore may lead to a selection effect. Another strong point of this study design is the economic evaluation from both national economic and statutory health insurance views. Patient reports on service use will provide the basis for estimating disease-related costs independently of funding agencies. In addition, health insurance claims data will be used to assess real costs for statutory health insurance.

The integrated care concept has been refined based on the results of the previous IVPOWER-study, which examined the efficacy of integrated care according to network mental health contracts. Fundamental changes were made with regard to participant enrolment and to the comparability of services across sites. An initial standardised assessment process regarding empowerment, unmet care needs, and psychosocial functioning was introduced to verify the need for such a comprehensive form of care by all community-based mental health service providers. Moreover, quality standards for GBV were set, and training activities across service providers were organised.

However, it is still to be assumed that service provision will vary across sites. As GBV is a complex intervention relying on good networking with local service providers, GBV depends on the available local service providers and their willingness to cooperate. Furthermore, it is not enough to define GBV’s individual components. Rather, the service providers’ processes and principles should be harmonised. Thus, differences in multiprofessional cooperation and the recovery orientation of GBV teams are assumed to impact GBV’s effectiveness. These aspects will be examined within the process evaluation, though the study is not designed to estimate site-specific effects. But when performing effectiveness analysis, the clusters of study sites will be taken into account in the covariance structure.

Another difficulty in this project is to avoid indirect changes in CAU by implementing GBV. GBV will be provided by teams working for community-based mental health service providers that offer a broad spectrum of services. Staff training and changes in infrastructure, especially communication channels, may also impact standard care. This applies especially to cases in which staff members are active in different services (e.g. GBV and outpatient sheltered living) at the same time. Nevertheless, this RCT should make it possible to demonstrate the added value of GBV, i.e. the additional care services such as case management, network discussions, and crisis services, even if the underlying standard care should improve in both groups.

